### Sample size {14}

The sample size calculation was based on VF data (primary outcome) from a published study [61], and from a retrospective analysis of the patient cohort at Grenoble-Alpes University Hospital (personal data). Bellusci et al. [61] showed that inferior VF defects varied from −11.7 ± 2.7 at diagnosis to 10.3 ± 3 dB (*n* = 5) at 6 months, with diffuse defects varying from −15.5 ± 7.4 to −16.4 ± 7.9 dB (*n* = 7) and central defects varying from −5.3 ± 0.7 to 4.8 ± 1.7 dB over the same timespan (*n* = 4). Consistently, in our retrospective cohort, the progression of inferior altitudinal VF defects (*n* = 14) showed an 11% deterioration in the mean deviation (MD) between 3 and 6 months (from −15.2 ± 9 initially to −15.8 ± 7.8 dB) and 21% worsening of the MD for superior altitudinal defects (*n* = 8, from −14.9 ± 4.2 dB initially to −17.08 ± 5.7 dB).

We hypothesised that the mean deviation at inclusion would be −15 ± 9 dB and that the treatment would provide a 40% improvement in the defect, i.e. a progression from −15 to −9 dB, while no change is expected in the placebo arm. A sample size of 36 patients per group would thus provide 90% power to detect such a difference using a general linear model, with a common standard deviation of 9, an alpha risk of 0.05 and with an *r*-squared for the covariate (VF at baseline) of 0.3. To take account of patients lost to follow-up and/or those with prematurely stopping the protocol (including interruptions related to the side effects of bosentan, evaluated at 20% of the sample, *n* = 14), a total of 86 patients need to be included (*n* = 43 per group).

This sample size should provide >90% power to detect a significant difference in the thinning of retinal nerve fibres, hypothesising a smaller reduction in RNFL thickness after treatment (reduction evaluated at −43% in the placebo arm patients versus −25% in patients treated with bosentan), using an ANCOVA.

### Recruitment {15}

All eligible patients attending one of the participating ophthalmology departments are proposed participation in this trial. The recruitment period began in August 2015, is ongoing and is expected to end in December 2022. The estimated rate of recruitment is 1 or 2 patients per month. In 2016, the study was stopped for 9 months due to a supply issue of bosentan and recruitment was slow in 2020 and 2021 due to COVID. In August 2022, 72 out of 86 patients had been recruited.

## Assignment of interventions: allocation

### Sequence generation {16a}

Centralised randomisation with computer-generated random numbers, stratified by study centre, is used to randomly assign patients who meet the inclusion criteria to the bosentan or the placebo group. A MEDSHARING IWRS (Interactive Web Response System) server is used for randomisation.

### Concealment mechanism {16b}

A MEDSHARING IWRS (Interactive Web Response System) secured server is used for randomisation.

### Implementation {16c}

The study investigator enrols participants and accesses the website using a personal ID and password during the inclusion visit and is thereby informed of the intervention assigned to the participant.

## Assignment of interventions: blinding

### Who will be blinded {17a}

The investigators, patients and the hospital pharmacies are blinded to the treatment allocated. Only the coordinating pharmacy is unblinded to the treatment batches sent to the participating centres. The bosentan and placebo tablets cannot be differentiated visually.

### Procedure for unblinding if needed {17b}

In case of a serious adverse event requiring medical intervention, unblinding is planned along with a declaration to the Clinical Trials Vigilance Unit. The investigator can obtain the unblinding directly from the IWRS website, although it is recommended that the centre contacts the sponsor and the coordinating investigator before proceeding to unblinding. The reason for the unblinding must be clearly mentioned in the source documents and in the case report form (eCRF).

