### Intervention description {11a}

The treatments are initiated after inclusion and randomisation according to the group to which the patient is assigned: Group 1: oral 125 mg bosentan twice a day (BD) (total dose, 250 mg/day); Group 2: oral placebo, BD. Treatments are administered for 8 weeks.

The coordinating pharmacy prepared the investigational medicinal products (IMP), obtained from Pharmascience Inc. Montréal, Québec. Masking of pms-BOSENTAN 125 mg and 62.5 mg tablets was done by overencapsulation in size #1 opaque capsules. Pms-BOSENTAN 125 mg placebo and pms-BOSENTAN 62.5 mg placebo are empty capsules overencapsulated in the same size #1 and colour opaque capsules. The coordinating pharmacy also performed the packaging and labelling of the IMP and matching placebo. Thus, IMPs and placebos are indistinguishable.

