**Fig. 2 Fig2:**
[figure not shown]
Schedule of enrolment, interventions and assessments for a patient included in the ENDOTHELION trial

Following randomisation, the first administration of the treatment is given in the ophthalmology department. Blood pressure (BP) is checked 4 h after this, corresponding to the plasma peak of bosentan according to the pharmacological data in the study by Weber et al. [59].

Patient monitoring/follow-up includes consultations at week 2, and at 1, 2, 3, 6, 12 and 24 months with one of the investigating ophthalmologists, during which several examinations are carried out: an ophthalmological examination (VA, VF, SD-OCT and fundus examination), a clinical examination searching for the adverse side effects of bosentan, an office-measurement of BP and a blood work-up including a haemogram and measurement of liver enzymes (until and including the month 2 visit). Self-measurement of BP is programmed during weeks 1 and 4 and the last week of treatment (week 8).

The primary endpoint is set at 3 months so as to assess the efficacy of bosentan before initiating treatment for OSAS, the recognised period when visual function usually stabilises, and papillary oedema disappears, proceeding to papillary atrophy. Contreras et al. [60] showed that at 1.5 months following the acute phase, the RNFL thickness of the affected eye was similar to that of the unaffected eye, indicating that the optic disc swelling had partly resolved. After this first period, atrophy of the optic nerve head became detectable, such that at the 3-month visit, the RNFL had thinned by 39%, compared to the contralateral normal eye [60]. Loss of retinal nerve fibre layers stabilised thereafter, with only 6% additional thinning at the 12-month visit. In another study, Hayreh et al. [57] estimated the median time to papillary oedema resolution was 7.9 weeks (IQR, 5.8–11.4 weeks).

In the present trial, at 3 months, the clinical examinations and laboratory analyses (including a study of endothelial function), the ophthalmological examinations (VA, VF, SD-OCT and fundus examination) and the blood work-up (with serum banking) performed at inclusion are repeated. A polysomnography is planned after the 3-month visit.

The visits at 6 and 12 months and the end-of-protocol visit at 24 months include an ophthalmological examination (VA, VF, SD-OCT and fundus examination). The quality-of-life questionnaire (VFQ-25) [58] is completed at the 3- and 12-month visits.

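### The unblinding rule is triggered by a serious event needing intervention, not by a need to know the allocation, and has no end date

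*Protocol article*

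**What the plan says.** All references are to the protocol article.

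- **Trigger, {17b}:** "In case of a serious adverse event requiring medical intervention, unblinding is planned". The same sentence couples this with a declaration to the vigilance unit.
- **Access, {17b}:** "The investigator can obtain the unblinding directly from the IWRS website". Prior contact is advised but not required: "it is recommended that the centre contacts the sponsor and the coordinating investigator before proceeding to unblinding". The reason has to be documented in the source records and the eCRF.
- **Who stays blind, {17a}:** "The investigators, patients and the hospital pharmacies are blinded to the treatment allocated".
- **Treatment period, {11a}:** "Treatments are administered for 8 weeks".
- **Follow-up, {13}:** "consultations at week 2, and at 1, 2, 3, 6, 12 and 24 months with one of the investigating ophthalmologists".
- **Monitoring board, {21a}:** the board may ask for unblinding in a way that keeps the allocation from both investigator and patient.
- **Safety reporting, {22}:** the sponsor judges whether a serious event was expected and makes the declarations to the authorities.

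**The concern.** The trigger has two parts: the event is serious, and it needs medical intervention. Neither part asks whether treating the patient depends on knowing if bosentan or placebo was given. Nor is there a time limit, so on its face the sentence covers an event in month 20 in the same way as one in week 3.

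The blind at stake is that of the investigators, the group from which the follow-up ophthalmologists are drawn. Perimetry and ETDRS acuity depend on patient effort and can respond to how the examination is conducted. VFQ-25 is self-reported. If serious events were more frequent in one arm, the loss of blinding would also be unequal between arms.

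**Working it through.** The document gives no figure to reproduce on this point. The check compares the text of the sections and then asks what can be said about size.

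**1. Does any section supply the missing criterion?**

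| Element of {17b} | Function | Limits unblinding to cases of need? |
|---|---|---|
| Serious event needing intervention | Trigger | No |
| Contact with sponsor and coordinating investigator | Advice | No |
| Recorded reason | Documentation after the decision | No |
| Time window | None stated | No |

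Section {17a} makes investigators blind and states no exception. Section {17b} is therefore the only place where the exception is defined, and it is defined by the event rather than by the need for the code.

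**2. Does the safety declaration require the site to be unblinded?** Section {17b} couples unblinding with the declaration. Section {22} gives the assessment and the declarations to the sponsor, and {21a} already has a route that keeps investigator and patient blind. The document's own arrangements therefore do not need the site to know the allocation for reporting.

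**3. When could the rule operate?** Inputs: treatment 8 weeks ({11a}); follow-up 24 months, which is 730.5 / 7 = 104.4 weeks.

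- On-treatment share of follow-up time: 8 / 104.4 = 7.7%.
- Post-treatment share: 96.4 / 104.4 = 92.3%.

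These are shares of time, not of events. Let k be the ratio of the on-treatment to the post-treatment event rate, which is an assumption. The share of events after treatment is 96.4 / (96.4 + 8k):

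| k | Share of events after treatment |
|---|---|
| 1 | 92% |
| 3 | 80% |
| 5 | 71% |
| 10 | 55% |

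The share falls to one half at k = 96.4 / 8 = 12.0. All of this assumes that the rule applies for the full 24 months.

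**4. How many before the primary endpoint?** Month 3 is 13.04 weeks and one year is 52.18 weeks. For an assumed constant rate r per patient-year, expected events in 86 patients by month 3 are 86 × r × 13.04 / 52.18:

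- r = 5%: 86 × 0.05 × 0.25 = 1.1.
- r = 20%: 86 × 0.20 × 0.25 = 4.3.

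Over 24 months the same rates give 86 × 0.05 × 2 = 8.6 and 86 × 0.20 × 2 = 34.4 events. These are events, not patients, and not all would meet the trigger or lead to a code break. They are illustrations only. If events cluster during treatment (k above 1), the count before month 3 rises, but those are the events for which the allocation is most likely to matter.

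**The case against.** **The wording can be read as permissive.** The section heading speaks of unblinding if needed, the investigator *can* obtain the code, prior contact is advised, and a reason is recorded. Consultation and a reason make little sense if every such event unblinds automatically, so *planned* may mean *provided for*. This stands as a fair reading. A reader might infer that every serious event will routinely be unblinded, and the document does not establish that. It also gives no criterion that rules the literal reading out, and sites could apply the sentence differently.

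**The size is not in the document.** This stands. A reader might infer a definite number of unblinded patients, or that most would be unblinded after the last dose. With no serious-event rate stated, both are assumptions. There is also a tension: an excess caused by the drug would cluster on treatment, while late events unrelated to the drug give little reason to expect imbalance between arms.

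**The bias path is partial.** This also stands. The text says one of the investigating ophthalmologists, so it cannot be claimed that the person who broke the code does the later examinations. It does not say who runs perimetry or acuity testing. Bias through VFQ-25 requires the patient to learn the allocation, and {17b} describes only the investigator obtaining it. OCT thickness is an instrument measurement, and visual field data face reliability limits ({18a}) and a check by an experienced ophthalmologist ({19}).

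**Direct access is normal.** Investigator access through the IWRS is an ordinary safety provision and is not a fault.

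**The article condenses a longer protocol.** Detailed code-break criteria may be there. The point here is not an omission, however: the article states a trigger, and states it too broadly.

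**Conclusion.** The point holds as a defect of wording with a modest potential for bias. The stated trigger does not depend on a need for the allocation and has no end date. Applied literally, it removes the investigator's blind in cases with no management benefit, against {17a}. The exposure falls mainly on visual field and acuity at 6, 12 and 24 months and, if the patient is told or gets cues, on VFQ-25 at 12 months.

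A reader might go further and conclude that the primary comparison is compromised. The document does not support that. The endpoint is automated perimetry at 3 months, and at the assumed constant rates only about 1 to 4 events would precede it. No number of affected patients, and no direction of bias, can be derived from the document.

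**What to change.** Reword the first sentence of {17b} so that the site breaks the code only where the investigator judges that knowing the allocation is needed to manage the event. That judgement stays with the investigator, and emergency access through the IWRS stays as it is.

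Add that, where the code is needed only for the safety declaration, the sponsor's vigilance unit obtains it without informing the site or the patient, following the model {21a} already uses for the monitoring board. From the eCRF entry already required, list site-unblinded patients by arm, with the date of unblinding.

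The cost is about a sentence of protocol text and a short listing. The change can still have effect: the abstract reports 72 patients included, of 86 planned, and 49 with complete follow-up. At most 86 − 49 = 37 patients (14 still to be recruited and up to 23 in follow-up) would come under the revised wording.

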## Data collection and management

### Plans for assessment and collection of outcomes {18a}

All the data from the consultations and the clinical examinations, constituting the source data, are entered and stored in an electronic CRF. Statistical analysis will only be performed after verification of data entry and of the consistency of the data.

The following *ophthalmological examinations* are performed during the study:VA assessed using the ETDRS (Early Treatment Diabetic Retinopathy Study) scale. Fluctuation of ± 5 ETDRS letters is considered to be nonsignificant;Average intraocular pressure values measured three times using a Goldmann tonometer in each eye;Central corneal thickness is measured using pachymetry in both eyes (only at the initial screening visit);Axial length of both eyes is measured with non-contact biometry (only at screening);Fundus examination and fundus colour retina imaging is done for in each eye (45 degrees) after pupillary dilation.

The ophthalmoscopic description includes the following: the topography of the papillary oedema optic disc swelling, the retinal oedema at the posterior pole, vertical cup/disc ratio and the size of the optic disc (for the non-affected eye, the measurement takes into account the type of examination lens used) as well as the state of any posterior vitreous detachment. At the screening visit, fundus images of the nine quadrants are taken, and then after one photo centred on the optic nerve and one centred on the macula.

At inclusion the *visual field* (VF) is evaluated using automated perimetry (Humphrey 30-2 SITA standard programme) for both eyes (the healthy eye first and then the affected eye), and repeated at 24-h time intervals. Goldmann perimetry is done if automated perimetry is not feasible. The VF is classified according to the type of defect (11 possible types [62]): diffuse, superior or inferior hemifield, superior or inferior arcade, superonasal, inferonasal, superotemporal, inferotemporal quadrant, central scotoma or concentric defect.

The quantitative analysis is based on the mean deviation in decibels (dB). The minimum significant change is 2 dB between two examinations so as to take into account learning and long-term fluctuations. The VF assessment is considered reliable if the rate of fixation loss, false negatives or false positives is less than 33%.

Given its availability in all the clinical sites, we selected to use the Cirrus OCT 5000 (Carl Zeiss Meditec, Dublin, CA, USA) for *Optical Coherence Tomography* (SD-OCT) with an acquisition protocol and RNFL thickness analysis, optic disc cube 200×200, study of the ganglion cell complex (GCC) and a macular cube 200×200 protocol, all with the healthy contralateral eye examined first. The measurement is validated if three good-quality images (signal power >6) are obtained.

The individual values of average RNFL thickness, either total or by quadrant (temporal, nasal, superior, inferior), measured in micrometres will be used for statistical comparisons. The OCT measurements of the optic disc size (diameter) and vertical cup/disc ratio of the contralateral eye will be compared. Besides RNFL thickness data, macular data are also acquired in order to detect subtle maculopathies or the presence of subretinal fluid. This also makes it possible to measure the central macular thickness (CMT) and macular ganglion cell-inner plexiform layer (GCC) thickness.

*Fluorescein and indocyanine green angiography* are performed to confirm optic disc swelling and allow to detect choroidal ischemia so as to differentiate arteritic anterior ischemic optic neuropathy from NAAION. If a patient is allergic to fluorescein, the angiography can be done using indocyanine green dye only.

*Ambulatory blood pressure monitoring* (ABPM) is done using an ambulatory blood pressure monitor is fitted during visit 1 between 08.30 am and 10.30 am and then removed and read the following day, at least 24 h after its installation. The device used is SPACELABS 90207 (validated by the British Heart Association and the Association for the Advancement of Medical Instrumentation). Blood pressure is measured every 15 min during the day and every 20 min at night.

Each recording is verified according to the following quality criteria: cuff size adapted to arm circumference (according to American Heart Association recommendations), calibration of the device (not more than 5 mmHg difference between the first measurement recorded by the device and a concomitant sphygmomanometric measurement of SBP and DBP), recording duration >24 h including at least 70% usable measurements with at least two exploitable measurements per time period (both night and day). SBP values > 260 mmHg or < 70 mmHg and DBP > 150 mmHg or < 40 mmHg are automatically eliminated. In case of inadequate measurements, we suggest refitting the device. The patients are requested to complete an activity form for the 24 h concerned by the recording.

The following parameters are collected: systolic blood pressure (SBP), diastolic blood pressure (DBP), mean blood pressure (MBP) and heart rate (HR), during the day (7.00 am to 10.00 pm) and during the night (10.00 pm to 7.00 am), including the night-time drop in SBP, DBP, MBP and HR.

For the *self-measurement of blood pressure* a blood pressure monitor (electronic OMRON MIT Elite Plus M10-IT, OMRON Healthcare Co. Ltd. Kyoto, Japan) is provided to all patients for the total duration of treatment (2 months). Patients are expected to perform two series of readings per day: in the morning before breakfast (and before taking the treatment) and at bedtime. They should take three readings 1 min apart at each session over a period of 3 consecutive days, during weeks 1, 4 and 8.

*Clinical blood pressure measurements* are made at each visit up to and including the 3-month visit, office-blood pressure in a seated position is measured after 10 min of rest (mean of three measurements taken 1 min apart). Resting heart rate is measured during the second BP measurement.

For *laboratory analyses*, an 8-mL fasted blood sample is taken during visits 1 to 4 to measure ASAT (IU/L), ALAT (IU/L), creatinine (μmol/L) and complete blood count. Two additional samples (to measure the HAb1c and homocysteine levels) are taken at visit 1.

Additional 7-mL blood samples are taken during the inclusion and post-treatment visit at month 3 (visit 5). The serum and plasma aliquots are anonymised and kept at −80°C for later complementary analyses (serum bank). No genetic analyses will be realised.

### Plans to promote participant retention and complete follow-up {18b}

The importance of attending all follow-up visits until the end of the trial is explained to all potential participants at the screening visit to ensure that only those who are able to commit to the entire protocol are included. The importance of adherence to the treatment is also explained. Appointments are organised by the local clinical research assistants (CRA) and investigators, who are responsible for organisation and communication with the patients.

### Data management {19}

Data monitoring and data management are realised on all of the eCRFs. Data from visual field and SD-OCT assessments are checked by an experienced ophthalmologist.

### Confidentiality {27}

This trial conforms to the reference methodology (MR-001) of the independent French Data protection agency (CNIL) endorsed by the trial sponsor (Grenoble-Alpes University Hospital). In practice, according to French law, patient data are anonymised when the patient is included in the study. Moreover, anonymisation and data protection are requested by the IRB and the study sponsor. Only one investigator in each centre has access to the individual patient identities linked to their identification numbers, kept in a secured server. Data entered in the e-crf is also stored in a secured server with a personal password required for access, which is restricted to the investigators and the study clinical research assistant only. The eCRF is managed by Medsharing (Fontenay Sous Bois, France).

### Plans for collection, laboratory evaluation and storage of biological specimens for genetic or molecular analysis in this trial/future use {33}

Blood samples are collected at all study visits up until the visit at 3 months for biological laboratory analysis of liver enzymes, inflammation markers and plasma levels of pre-proendothelin (Fig. 2). In addition, blood samples are taken at inclusion and the M3 visit for biobanking. Serum and plasma aliquots are anonymised and kept at −80°C for later complementary analyses (serum bank). No genetic analyses are planned.

